# Effects of Melatonin on Glycemic Variability in Type 2 Diabetes Mellitus: Protocol for a Crossover, Double-Blind, Placebo-Controlled Trial

**DOI:** 10.2196/47887

**Published:** 2023-08-16

**Keywords:** type 2 diabetes mellitus, glycemic control, melatonin, randomized controlled trial, cross-over studies, T2DM, glucose, glycemic variability, circadian rhythm

## Abstract

**Background:**

Glycemic variability is recognized as a significant factor contributing to the development of micro- and macrovascular complications in individuals with type 2 diabetes mellitus (T2DM). Numerous studies have shown that melatonin, a hormone involved in regulating various biological rhythms, including those related to glucose regulation, such as hunger, satiety, sleep, and circadian hormone secretion (ie, cortisol, growth hormone, catecholamines, and insulin), is deficient in individuals with T2DM. This raises an important question: Could melatonin replacement potentially reduce glycemic variability in these patients? This warrants investigation as a novel approach to improving glycemic control and reducing the risk of complications associated with T2DM.

**Objective:**

We aimed to investigate whether melatonin replacement in individuals with T2DM who supposedly have melatonin deficiency can positively impact the regulation of insulin secretion rhythms and improve insulin sensitivity, ultimately resulting in a reduction in glycemic variability.

**Methods:**

This study will use a crossover, randomized, double-blind, placebo-controlled trial design. Patients with T2DM in group 1 will receive 3 mg of melatonin at 9:00 PM in the first week, undergo a washout period in the second week, and receive a placebo in the third week (melatonin-washout-placebo). Group 2 will be randomized to receive a placebo-washout-melatonin sequence (3 mg). Capillary blood glucose levels will be measured at 6 different times before and after meals during the last 3 days of the first and third weeks. The study aims to compare the mean differences in blood glucose levels and the coefficient of glycemic variability in patients receiving melatonin and placebo during the first and third weeks. After analyzing the initial results, the number of needed patients will be recalculated. If the recalculated number is higher than 30, new participants will be recruited. Thirty patients with T2DM will be randomized into the 2 groups: melatonin-washout-placebo or placebo-washout-melatonin.

**Results:**

Participant recruitment took place between March 2023 to April 2023. In all, 30 participants were eligible and completed the study. We expect that patients will show different glycemic variability on the days they receive placebo or melatonin. Studies on melatonin and glycemic control have shown both positive and negative results. We hope that there will be a positive outcome regarding glycemic variability (ie, a reduction in glycemic variability), as melatonin has a well-described chronobiotic effect in the literature.

**Conclusions:**

This study aims to determine whether melatonin supplementation can effectively reduce glycemic variability in patients with T2DM. The crossover design is necessary due to the multiple variables involved in the circadian variations of glucose, including diet, physical activity, sleep parameters, and pharmacological treatments. The relatively low cost of melatonin and its potential role in reducing the severe complications associated with T2DM have motivated this research effort. Furthermore, the indiscriminate use of melatonin in current times makes conducting this study essential to evaluate the effect of this substance in patients with T2DM.

**Trial Registration:**

Brazilian Registry of Clinical Trials RBR-6wg54rb; https://ensaiosclinicos.gov.br/rg/RBR-6wg54rb

**International Registered Report Identifier (IRRID):**

DERR1-10.2196/47887

## Introduction

Despite recent advances in medical technology and treatments for type 2 diabetes mellitus (T2DM), the prevalence of this disease is still increasing exponentially worldwide [1]. According to the International Diabetes Federation, the number of adults with T2DM globally was expected to rise to 463 million in 2019 and 700 million by 2045, with a significant impact on public health, society, and the economy [2]. Effective treatment of T2DM is crucial in avoiding complications and improving overall health outcomes for patients. In recent years, the management of T2DM has evolved significantly due to the discovery of new therapeutic targets and the development of new drugs with different mechanisms of action [3]. Additionally, nondrug interventions that impact glycemic control have become increasingly important in the management of T2DM [4,5]. Dietary modification, physical activity, weight management, and stress management have long been recommended. In addition to lifestyle modifications and medication, the role of good quality sleep in managing T2DM has become increasingly recognized by health care professionals. The American Diabetes Association’s 2017 position statement underscored the significance of adequate sleep in the management of T2DM and brought attention to the detrimental effect that sleep disturbances can have on glycemic control [6]. Melatonin, a hormone linked to the circadian rhythm, may be the pathophysiological link between sleep changes and glycemic control [7]. This hormone synchronizes our waking, sleeping, hunger, and satiety times, as well as other biological functions, such as insulin secretion. Previous studies found that melatonin production is reduced in T2DM [8-10]. While some papers have suggested that melatonin replacement may have benefits for glycemic control, the results of these studies have been conflicting, with some studies not showing significant benefits [11-14]. How can such differences be explained? The impact of melatonin on glycemic control may depend on several factors, including the timing and duration of use, as well as individual genetic variations, such as *MT2* melatonin receptor polymorphisms [15,16] Mutations in the *MT2* receptor gene have been associated with altered glucose metabolism and insulin sensitivity and may impact the effectiveness of melatonin supplementation in improving glycemic control. Some studies have suggested that individuals with *MT2* receptor mutations may experience an increase in glycohemoglobin levels following melatonin use, unlike those without this mutation.

Assessing variations in glucose throughout the day, instead of just the average glycohemoglobin level, is an important aspect of investigating the potential impact of melatonin on glycemic control. In this work, we will not evaluate the role of melatonin in average glucose (glycohemoglobin) level, but on variations in glucose level throughout the day. Our proposal is to determine whether melatonin influences the circadian rhythm of glucose in patients with T2DM. Currently, no study has evaluated whether melatonin has such a role.

Glycemic variations throughout the day depend on central and peripheral control of insulin secretion and sensitivity. Previous studies have linked the action of melatonin on *MT1* and *MT2* receptors to insulin secretion and sensitivity [17]. Our hypothesis is that melatonin replacement in people with T2DM who are melatonin deficient may have a positive role in the regulation of insulin, cortisol, and the rhythms of other secretions. If this hypothesis is correct, melatonin replacement may reduce the range of blood glucose variation throughout the day. It has already been demonstrated that wide circadian glucose variation in patients with diabetes mellitus can be a stress and inflammation factor and lead to chronic complications of the disease that occur when glycohemoglobin is elevated [18,19]. Thus, this study asks, Could melatonin replacement in these melatonin-deficient patients attenuate these glycemic oscillations? The objective of this research project is to assess whether melatonin supplementation can reduce glycemic variations throughout the day in patients with T2DM.

## Methods

### Study Design

This prospective, crossover, double-blind, randomized, placebo-controlled study was approved by the ethics committee of the Federal University of Minas Gerais. The study will be conducted at an endocrinology outpatient clinic run by the research physician (WM) in the city of Belo Horizonte, Brazil. Thirty patients will participate in the initial phase of this work. These patients will be randomized to 2 groups: a placebo-washout-melatonin (3 mg) group, which will receive a placebo for 7 days, followed by 7 days without the study medication (washout period) and 7 days of melatonin (3 mg); and group 2, the melatonin-washout-placebo group, which will receive melatonin (3 mg) for 7 days, followed by 7 days without the study medication (washout period) and 7 days of placebo. When 15 patients are allocated to one of the possible intervention orders (placebo followed by melatonin or melatonin followed by placebo), 15 patients will be allocated to the other, not-yet-complete intervention order. Patients will be instructed to use the study medication at 9:00 PM. Patients will receive guidance on diet and physical activity to be followed during these 3 weeks. On the fifth, sixth, and seventh days of the first week and the fifth, sixth, and seventh days of the third week, the patients will use a glucometer to monitor fasting capillary blood glucose before breakfast, 2 hours after breakfast, before lunch, 2 hours after lunch, before dinner, and 2 hours after dinner. The primary outcome analyzed in this study will be the variability of pre- and postprandial glycemia. The result will be compared between 2 periods: with placebo and with melatonin.

### Blinding

Medicine bottles containing melatonin or placebo will be numbered 1 and 2, not necessarily in that order. The individual responsible for assigning the numbers will be the sole person with knowledge of which bottles contain melatonin and which contain placebo. All other people involved in this project (patients, medical researchers, statisticians, and assistant personnel) will be blind in relation to the substances. Upon completion of the statistical analysis, the researchers will be informed as to which bottle contained melatonin and which contained placebo. Figure 1 shows a flowchart of the study.

**Figure 1 figure1:**

Flowchart.

### Glycemic Variability and Crossover Studies

Crossover studies present an advantage over parallel group studies: comparing 2 or more interventions in the same individual reduces possible biases related to differences between groups. Such a design is suitable for chronic diseases and for testing drugs that control a disease but do not cure it. Curing a disease in one period of the study would make it meaningless to use another drug or even a placebo in the following period. When studying an outcome that is influenced by several variables, this design allows for a more reliable comparison with a smaller sample. This is the case for assessing glycemic variability in patients with T2DM. Glycemic variability in patients with T2DM can be influenced by several factors, including medications, duration of diabetes, age, diet, and physical activity. In the evolution of the treatment of diabetes mellitus, there has been an effort to develop drugs that reduce variability in glycemia: dipeptidyl peptidase 4 (DPP-4) inhibitors, GLP1 (glucagon-like peptide 1) analogues, and ultra-slow insulins. Patients with T2DM are treated with a diverse combination of the available drugs. For this reason, pairing groups for a comparison of glycemic variability would be a complex task. Added to this are individual differences in diet and physical activity. Thus, a crossover study is more suitable for the purpose of this work.

### Melatonin and the Carryover Effect in Crossover Studies

Crossover studies should include an adequate washout period, that is, a period in which there is a break from the initial intervention until the beginning of the next intervention. In this work, we propose a period of 1 week for the washout. Questions to examine include whether that time is adequate and whether effects of the initial intervention in the first week remain in the third week. As melatonin has a short half-life (10 to 60 minutes), we believe that its influence will not be present in the third week of the study in the group that uses it initially; a washout period of 1 week thus seems sufficient [20]. Therefore, after a week without using any substance, the initial intervention will not influence the proposed intervention in the third week.

### Glycemic Variability

Glycemic variability refers to fluctuations in blood glucose levels over time. It can be short-term, in self-monitored evaluations of (pre- and postprandial) capillary blood glucose; it can also use the gold standard method, continuous blood glucose monitoring, in which nocturnal blood glucose fluctuations are recorded every 5 minutes [21,22]. There is little correlation between the average variability in glycemic amplitude measured by continuous glucose monitoring and by self-monitoring; however, the latter method can be used for structured assessments of short-term glycemic variability in a day and between different days. The calculation of glycemic variability by this method can also be performed using SDs or even the coefficient of variation. A glycemic variation coefficient of less than 36% is considered level E evidence to separate stable from unstable glycemic control [21]. This measure is considered most effective to assess glycemic variability; however, comparing glycemia between different days is more effective with the mean of daily differences (MODD). This measure is obtained by determining the difference in blood glucose measured at the same time in a 24-hour interval. An additional computer program is used for this measurement, and it cannot be obtained only by continuous capillary blood glucose monitoring devices [21]. In this work, we will use pre- and postprandial capillary glycemia monitoring to determine the glycemic variability of patients with T2DM. In addition to the low cost of the method, we believe that this method gives the work an aspect of a real-life study and therefore greater clinical relevance.

### Inclusion and Exclusion Criteria

Patients will be included in this project according to the following criteria: (1) T2DM duration more than 1 year, (2) age greater than or equal to 40 years, (3) family history of T2DM, and (4) glycohemoglobin between 7% and 10%. Inclusion criterion 1, a T2DM duration of more than 1 year, was chosen because in the first year after diagnosis, patients might not yet have achieved baseline glycemic control. Some patients may have significant improvement in beta-cell glucotoxicity in the first year, with reduced blood glucose levels, and therefore have very wide blood glucose variations from one week to the next because of this improvement. Inclusion criterion 2, the age limit, was established based on the fact that most individuals with T2DM are aged over 40 years. In this way, we avoid including individuals who have autoimmune or genetic diabetes in the study. Item 3 is important because it further homogenizes our patients. We know that T2DM has a strong hereditary component, unlike other types of diabetes. Item 4, limiting the glycohemoglobin value range to 7% to 10%, was established with the objective of homogenizing glycemic variability among our patients, as it is known that glycemic variability increases with an increase in glycohemoglobin.

The following patients will be excluded from this study: (1) pregnant women, (2) patients who have recently (within 3 months) used corticosteroids or other hyperglycemic medications, (3) patients who have conditions that significantly alter glycemic stability (such as renal failure, recent acute coronary syndrome, and other diseases, such as cancer and liver failure). Also excluded will be (4) patients who refuse to participate in this research at any point and (5) patients who have uncontrolled diabetes with symptoms of polydipsia, polyuria, or weight loss that require other measures, such as the use of insulin for glycemic control, in addition to diet, physical activity, and medications already in use. Finally, we will exclude from this study (6) patients at high risk for severe sleep apnea, (7) patients with depression, (8) patients with alternating work shifts, and (9) patients who have epilepsy, a condition that can worsen with the use of melatonin.

Most of these exclusion criteria function to limit conditions that generate very high glycemic variability. It is unlikely that the use of melatonin will be able to reduce glycemic variability induced by corticoids, for example. Patients at high risk for sleep apnea, patients with depression, and patients with alternating work shifts were excluded due to studies that show the negative influence of these conditions on glycemic control. Specific studies with these populations seem more adequate for the purpose proposed here.

### Ethical Aspects

Participants involved in this study will be required to sign an informed consent form that has been drafted in compliance with the Declaration of Helsinki [23]. The wording of the consent form was initially sanctioned, together with the entire project outlined herein, by the ethics committee of the Federal University of Minas Gerais (CAAE: 31990720.7.000.5149). The invitation to participate in this study will be extended during routine consultation at the office of an endocrinology physician (WM). Participants, if they meet the inclusion criteria, will be volunteers. There will be no payment. All research objectives, as well as potential risks pertaining to the use of melatonin, will be explained. We will emphasize, however, that melatonin is a low-risk substance with few side effects. A possible risk is daytime drowsiness, but this is unlikely given the very short half-life of the drug and the low dose used.

### Randomization

Patients will be randomized into two groups. Group 1 will use the substance contained in bottle 1 in the first week, will not use any substance in the second week (the washout period), and will use the substance contained in bottle 2 in the third week. Group 2 will use the substance contained in bottle 2 in the first week, will not use any substance in the second week (the washout period), and will use the substance contained in bottle 1 in the third week.

Patients will be divided into these groups according to the result of rolling a die. Those who roll a number from 1 to 3 will be in group 1, while those who roll a number from 4 to 6 will be in group 2. When the number of participants in a group reaches 15, patients will be automatically allocated to the other group until it includes 15 participants. The project researcher will know which patients will use bottle 1 or 2 in the first and third weeks but will not know which bottle contains placebo and which contains melatonin.

### Interventions

Patients will use melatonin in the first week and placebo in the third week or placebo in the first week and melatonin in the third week, according to the randomization described. On days 5, 6, and 7 of the first and third weeks of the study, patients will measure fasting capillary blood glucose levels 2 hours after breakfast, before lunch, 2 hours after lunch, before dinner, and 2 hours after dinner. Patients will also receive guidance on diet and physical activity to be followed during these 3 weeks. In the second week, patients will undergo a washout period. At the end of the study, the patients will return to the office with their capillary blood glucose results. At this point, they will be asked whether they experienced excessive daytime sleepiness at any point in the study and whether they suspected at any time whether a substance was the placebo or melatonin.

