### Procedures

Patients with T2DM will be selected to take part in this study during routine consultations held in an outpatient endocrinology clinic. At the end of the consultation, the endocrinologist, when verifying that the patient meets the inclusion criteria, will ask the patient if they are interested in participating in research on diabetes and melatonin. This question will be followed by reading the informed consent form. All stages of the research will be explained to the patient. This includes the research period, the use of a placebo substance and melatonin, the need to perform capillary blood glucose measurement 6 times a day for 3 days in the first week and 3 days in the third week, the washout period, and the delivery of capillary blood glucose results after the 3 weeks of the project. If the patient agrees to participate in the project, the researcher will ask them to sign the free and informed consent form. A copy of this form will be given to the patient. Next, the researcher will ask the patient to roll a die. Patients who roll a number from 1 to 3 will be in group 1 and will be included in the group that uses the following sequence: bottle 1, washout, bottle 2. Those who roll a number from 4 to 6 will be included in group that uses the following sequence: bottle 2, washout, bottle 1. After allocating the patient to one of the groups, the project researcher will fill in the research record, which will contain the epidemiological, clinical, and laboratory data of the patient, including age, gender, duration of diabetes, history of epilepsy, insulin use (or not), STOP-Bang (snoring, tiredness, observed apnea, high blood pressure, BMI, age, neck circumference, and gender) questionnaire results, weight, height, BMI, abdominal circumference, and glycohemoglobin value. After this step, the patient will be guided on the diet and physical activity regimens to be carried out during the 3 weeks of the project. Patients will be instructed to perform 30 minutes of physical activity 5 times a week during the 3 weeks of the project. After this guidance, patients will receive a glucometer, strips for measuring capillary blood glucose, and lancets to take home. In addition, patients will be given a form to record capillary blood glucose values. At the end of the third week, the patient will return with the blood glucose values.

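### Daytime sleepiness is asked once, at study end, for all three weeks together, so the answer as described gives no melatonin-versus-placebo comparison; the treatment-guess question does not fix which bottle or which guess is recorded.

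*Protocol article*

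**What the plan says.** All references are to the Protocol article, Methods.

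- **Timing.** Interventions places the questions at the return visit: "At the end of the study, the patients will return to the office with their capillary blood glucose results". Procedures describes one return: "At the end of the third week, the patient will return with the blood glucose values".
- **Sleepiness.** At that visit "they will be asked whether they experienced excessive daytime sleepiness at any point in the study and whether they suspected at any time", where the last words open the second question.
- **Treatment guess.** In full, that second question is "whether they suspected at any time whether a substance was the placebo or melatonin".
- **Home record.** Procedures says that "patients will be given a form to record capillary blood glucose values". No symptom record is described.
- **Why sleepiness is asked.** Ethical Aspects states: "A possible risk is daytime drowsiness", and adds that it is unlikely. The article also mentions epilepsy as a condition that melatonin can aggravate, but those patients are excluded.
- **Blinding.** Apart from the person who numbers the bottles, everyone involved "will be blind in relation to the substances". Each bottle carries the number 1 or 2.

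Neither question is listed under Primary and Secondary Outcomes or given an analysis under Statistical Analysis.

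**The concern.** A crossover lets each patient serve as their own control, for side effects as well as for glucose. That advantage is lost when a symptom is asked for the study as a whole, because the melatonin week, the washout week and the placebo week are merged into one answer. The article calls drowsiness unlikely, and the only tolerability question it describes cannot, as worded, test that statement against placebo.

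The guess question matters for another reason. Patients measure and write down their own glucose at home, and the Limitations section accepts that diet and activity may change between weeks 1 and 3. A patient who recognised melatonin could behave differently in that week. This question is the only check on blinding described, and a bare yes to having suspected something does not show whether the suspicion was right.

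**Working it through.** The plan gives no figure to reproduce here. The check is one of wording, plus a short calculation on assumed rates.

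**1. What a whole-study answer can show.** Let pM, pW and pP be the probabilities of sleepiness in the melatonin, washout and placebo weeks. If the weeks are independent, the chance of a yes for the study as a whole is

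P(yes) = 1 - (1 - pM)(1 - pW)(1 - pP).

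The rates below are assumed, since the documents give none:

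| Scenario | pM | pW | pP | P(yes) |
|---|---|---|---|---|
| Melatonin causes sleepiness | 0.20 | 0.05 | 0.05 | 1 - 0.80 × 0.95 × 0.95 = 0.278 |
| Same excess on placebo | 0.05 | 0.05 | 0.20 | 1 - 0.95 × 0.95 × 0.80 = 0.278 |
| No treatment difference | 0.128 | 0.05 | 0.128 | 1 - 0.872 × 0.95 × 0.872 ≈ 0.278 |

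The formula is unchanged when pM and pP are exchanged, so no choice of rates separates the two substances. Independence is only a convenience: a yes means sleepiness in at least one week, and that is unaffected by which week carries the melatonin label. Comparing groups 1 and 2 does not help, because both groups take both substances.

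**2. How wide the uncertainty is.** Suppose, purely as an illustration, that 6 of the 30 patients answer yes and no week is recorded. At one extreme all 6 were affected on placebo and none on melatonin: (0 - 6)/30 = -20 percentage points. At the other, all 6 were affected on melatonin and none on placebo: (6 - 0)/30 = +20 points. Some or all of the 6 might belong only to the washout. More patients would not remove this ambiguity, because it comes from the form of the question.

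**3. What the guess question can show.** Its object is a substance. Interventions and Randomization together give each patient two numbered bottles, each used in one known week. A guess such as bottle 1 being melatonin can therefore be written down at the final visit and checked after unblinding. Nothing is taken in the washout, so washout is not a possible answer. What the text leaves open is whether the bottle and the direction of the guess are recorded. A guess about the first bottle also rests on recall from two weeks earlier, after both bottles have been tried.

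**4. What weekly recording would yield.** The paired comparison of sleepiness uses only patients who report it in one treatment week and not in the other. With the exact two-sided McNemar test, 5 such patients all in one direction give 2 × (1/2)^5 = 0.0625, and 6 give 2 × (1/2)^6 = 0.031. With about 30 patients the result should be read as descriptive.

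**The case against.** **The article is condensed and shows no question form.** A follow-up about which week may be asked after a yes. This stands in part. A follow-up is neither stated nor excluded, so a reader who infers that the trial can never attribute sleepiness to a treatment goes beyond the text. Yet the article does not simply omit the procedure. It fixes one asking, at the end, over the whole study, and describes no other record. A follow-up at that visit would also rest on recall of up to three weeks.

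**The guess is tied to a substance.** This stands. A reader might infer that the guess, like sleepiness, is lost across melatonin, placebo and washout. The wording does not support that, for the reasons given in step 3 of the working.

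**Neither item is an outcome, and the aim is glycemic variability.** This stands as a limit on importance. It does not excuse a tolerability question that cannot inform on the treatment it concerns.

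**The 6 of 30 is invented.** It is an illustration of the ambiguity, not a measured error in the plan.

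**Thirty patients have already finished, so a new form is too late.** This stands for those patients. The Sample Size section provides for further recruitment if the recalculated number exceeds 30, and the change can apply to those patients.

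**Conclusion.** The point holds for sleepiness as the procedure is described: one pooled answer per patient gives no melatonin-versus-placebo comparison, although the crossover could supply one within each patient. For the guess, the point is narrower: the text fixes that suspicion is asked about, but not that the bottle and the guess are recorded.

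The size cannot be stated from the documents. With 6 unattributed yes answers in 30, the compatible difference runs from -20 to +20 points. The conclusion rests on the assumption that no follow-up by week is asked; if one is, the sleepiness defect shrinks to a problem of recall. The consequence is confined to tolerability and the check of blinding. Nothing here shows that blinding failed or that the primary glucose comparison is biased. The change is worth making because it costs so little.

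**What to change.** For any patients recruited after the sample size recalculation:

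- Add one yes/no item, excessive daytime sleepiness this week, to the existing home form, to be completed at the end of weeks 1, 2 and 3. Including week 2 keeps washout symptoms apart.
- Compare the melatonin and placebo weeks as paired data (exact McNemar), labelled descriptive.
- At the final visit, record the guess for each bottle as melatonin, placebo or don't know, and tabulate it against the actual content after unblinding. Leaving this to the final visit avoids drawing attention to the bottle's identity before the second treatment week.

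For the 30 patients who have finished, report sleepiness by week only where it was recorded that way. Otherwise state that it is not attributable to treatment, so that a pooled count is not read as evidence on melatonin's tolerability.

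The cost is three short entries, one of them in a week with no glucose readings, and one small table. Patient burden rises slightly, and the power of the sleepiness comparison will be low.
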